## Abstract

**Introduction:**

Chronic stable angina is common and disabling. Cardiac rehabilitation is routinely offered to people following myocardial infarction or revascularisation procedures and has the potential to help people with chronic stable angina. However, there is insufficient evidence of effectiveness and cost-effectiveness for its routine use in this patient group. The objectives of this study are to compare the effectiveness and cost-effectiveness of the ‘Activate Your Heart’ cardiac rehabilitation programme for people with chronic stable angina compared with usual care.

**Methods and analysis:**

ACTIVATE is a multicentre, parallel-group, two-arm, superiority, pragmatic randomised controlled trial, with recruitment from primary and secondary care centres in England and Wales and a target sample size of 518 (1:1 allocation; allocation sequence by minimisation programme with built-in random element). The study uses secure web-based allocation concealment. The two treatments will be optimal usual care (control) and optimal usual care plus the ‘Activate Your Heart’ web-based cardiac rehabilitation programme (intervention). Outcome assessment and statistical analysis will be performed blinded; participants will be unblinded. Outcomes will be measured at baseline and at 6 and 12 months’ follow-up. Primary outcome will be the UK version of Seattle Angina Questionnaire (SAQ-UK), physical limitations domain at 12 months’ follow-up. Secondary outcomes will be the remaining two domains of SAQ-UK, dyspnoea, anxiety and depression, health utility, self-efficacy, physical activity and the incremental shuttle walk test. All safety events will be recorded, and serious adverse events assessed to determine whether they are related to the intervention and expected. Concurrent economic evaluation will be cost–utility analysis from health service perspective. An embedded process evaluation will determine the mechanisms and processes that explain the implementation and impacts of the cardiac rehabilitation programme.

**Ethics and dissemination:**

North of Scotland National Health Service Research Ethics Committee approval, reference 21/NS/0115. Participants will provide written informed consent. Results will be disseminated by peer-reviewed publication.

**Trial registration number:**

ISRCTN10054455.

STRENGTHS AND LIMITATIONS OF THIS STUDYPragmatic randomised controlled trial of an established cardiac rehabilitation programme for individuals with chronic stable angina, with unblinded participants and rehabilitation providers.Concurrent economic evaluation with a health service perspective.Embedded process evaluation to determine the mechanisms and processes that explain the implementation and impacts of the enhanced rehabilitation programme.The web-based intervention may not be acceptable to some people, but a paper version is available.

## Introduction

Angina is chest pain usually caused by atherosclerosis of the coronary arteries, which restricts blood flow to the myocardium, especially when oxygen demand is increased during exercise. Angina is defined as stable if chest pain occurs predictably on physical exertion, or with emotion, and settles promptly with rest or after taking sublingual nitrate medication. Affected individuals have an increased risk of acute coronary events such as myocardial infarction (MI).^1^ Management consists of behaviour change advice to reduce risk factor profile, drug treatment and revascularisation procedures.^2 3^

Cardiac rehabilitation is routinely offered to patients following MI, or revascularisation procedures, and consists of co-ordinated activities to improve the underlying cause and restore optimal functioning and slow, or reverse, disease progression.^4^ The most prevalent components of cardiac rehabilitation are behaviour change and exercise training, but comprehensive cardiac rehabilitation programmes also include education, interventions to improve mental health, involvement of friends and family members and the development of long-term strategies beyond participation in the cardiac rehabilitation programme. Despite international guidance,^2 5^ such programmes are not offered routinely to people with chronic stable angina.^6^ In the UK, the National Institute for Health and Care Excellence (NICE) does not support cardiac rehabilitation in this group until stronger evidence of effectiveness and cost-effectiveness is available.^3^ Although there is a good evidence for the effectiveness of cardiac rehabilitation for heart failure,^7^ or following MI or revascularisation procedures,^8^ rates of uptake and long-term adherence are low, especially in women, ethnic minority groups, and in areas of high deprivation.^6^

A systematic review of exercise-based cardiac rehabilitation for adults with stable angina,^9^ identified seven randomised controlled trials (RCTs) (n=581) with high risk of bias. It found low-quality evidence that cardiac rehabilitation resulted in a small improvement in exercise capacity compared with usual care with standard mean difference 0.45 (95% CI 0.2 to 0.7), and uncertainty about the effect on all-cause mortality, acute MI, cardiovascular-related hospital admissions, quality of life and cardiac rehabilitation-related adverse events. These RCTs were small in size and recruited mainly white middle-aged men. More evidence is needed from under-represented groups including women, older age groups, ethnic minorities and those with comorbid conditions. Web-based programmes might increase the reach of cardiac rehabilitation, and there has been one small RCT (n=94) of such a programme (‘Activate Your Heart’), which demonstrated that it was possible to provide cardiac rehabilitation to people with chronic stable angina.^10^ Trial methods were feasible in terms of recruitment, retention and outcome measurement. After 6 months, there were statistically significant lower levels of angina frequency, but a larger RCT is needed to test longer-term effectiveness and cost-effectiveness.

‘Activate Your Heart’ has the potential to improve physical and mental health with minimal risk. There may be a risk of injury or provoking an episode of angina when exercising, however, the physical activity goals are carefully graded and the programme has an excellent safety record.^10^

### Aims and objectives

We aim to assess whether a web-based cardiac rehabilitation programme can improve the health of people with chronic stable angina, whether it is good value for money and delivered as intended.

The primary objective is to determine the effectiveness of the ‘Activate Your Heart’ web-based cardiac rehabilitation programme (or a paper version for those who prefer or who do not have internet access or device), for people with chronic stable angina compared with usual care in terms of angina-related health status, at 12 months’ follow-up.

Secondary objectives:

To estimate the cost-effectiveness of the cardiac rehabilitation programme for people with chronic stable angina compared with usual care in a cost–utility analysis with a health service perspective.To investigate the mechanisms and processes that explain the implementation and impacts of the cardiac rehabilitation programme in the intervention group and usual care in the control group.To identify the barriers and facilitators of uptake and completion of the rehabilitation programme with a focus on equity.

## Methods and analysis

### Trial design

ACTIVATE is a multisite, parallel-group, two-armed, superiority RCT with 1:1 allocation, stratified by gender and recruitment site (figure 1). A pragmatic RCT of effectiveness compared with usual care, with blinded outcome assessment and statistical analysis; unblinded participants and rehabilitation providers. An internal pilot phase will assess feasibility. There will be a concurrent economic evaluation with a health service perspective. An embedded process evaluation will use mixed methods to examine the mechanisms and processes that explain the implementation and impacts of the enhanced rehabilitation programme, including an examination of barriers leading to health inequities. The Health Inequalities Assessment Toolkit (www.hiat.org.uk) informed trial design. The RCT was registered on 16 September 2021 (ISRCTN10054455). Trial registration data can be found in online supplemental appendix 1.

10.1136/bmjopen-2024-084509.supp1Supplementary data

**Figure 1 F1:**
[figure not shown]
ACTIVATE participant flow chart.

### Trial setting and selection of sites/clinicians

Participants will be recruited from primary and secondary care in areas of England and Wales with high disease burden and socioeconomic deprivation. Many of these areas include high proportions of ethnic minority groups. The web-based rehabilitation intervention (or paper version) will be delivered in the community.

### Trial population

#### Inclusion criteria

Adults with chronic stable angina with at least two out of three of the following features: constricting central chest pain, precipitated by exertion or emotional stress, relieved by rest or glyceryl trinitrate spray.Evidence of myocardial ischaemia from either a medical history of acute coronary syndrome, MI or revascularisation procedure at least 12 months previously; or from imaging studies such as invasive coronary angiography, CT angiography or myocardial perfusion testing.Revascularisation procedures not planned and managed with medical treatments only, including people with previous MI, or previous revascularisation procedure who may have attended cardiac rehabilitation in the past.

#### Exclusion criteria

History of MI, revascularisation or cardiac rehabilitation participation within the last 12 months.Significant comorbidities (as deemed by the person confirming eligibility) that would limit participation in the exercise-based rehabilitation programme.Refractory angina on maximal medical therapy.

### Trial treatment/interventions

We plan to compare web-based cardiac rehabilitation in addition to optimal usual care (intervention) with optimal usual care alone.

#### Optimal usual care

Usual care will be optimised in all participants. All participants will be seen by their general practitioner or cardiology team, using a protocol informed by NICE guidance^3^ to ensure that all are receiving optimal care. Considering the pragmatic nature of the proposed RCT, no restrictions will be placed on usual care. NICE guidance^3^ recommends that patients with chronic stable angina receive adequate information and support, lifestyle advice about smoking, exercise, diet and weight control. Episodes of angina should be treated with short-acting nitrate medication. Antianginal drug treatment to prevent episodes of angina consists of a beta-blocker or calcium channel blocker in the first instance; second-line drugs (such as ivabradine, ranolazine) will be used as needed. In addition, drugs for secondary prevention of cardiovascular disease such as MI or stroke, include aspirin, ACE inhibitor (especially if diabetes is present), statins in line with NICE guidance (and treatment targets) on lipid modification^11^ and antihypertensives in line with NICE guidance (and treatment targets) on hypertension.^12^

Concomitant medication will be recorded as part of the health economic data collection. There are no restrictions on any medications. Participants will not have participated in a cardiac rehabilitation programme over the previous 12 months, but other schemes such as smoking cessation, exercise referral and weight management schemes may be available and accessible to participants. Where participants have engaged in one or more of these it will be recorded.

#### Cardiac rehabilitation intervention

Usual care will be optimised as described above. In addition, participants in the intervention arm will be given access to ‘Activate Your Heart’ (www.activateyourheart.org.uk), which is an online interactive, secure and password-protected website designed for participants to use at home. The programme was coproduced with healthcare professionals, patients/members of the public and software designers. The programme aims to deliver the five core components described by the British Association for Cardiovascular Prevention and Rehabilitation: health behaviour change and education, lifestyle risk factor management, medical risk factor management, psychosocial health and long-term management.^4^ The programme uses the following behaviour change techniques: goal setting, self-monitoring, feedback on behaviour, graded tasks, social reward, providing information about health consequences and reducing negative emotions. The programme is tailored to individual need, organised in four stages, which can be completed in 8 weeks, but access to the site and its features continues for 12 months. Before beginning the programme, each participant sees a member of cardiac rehabilitation staff who provides training on the website either face-to-face, or remotely by telephone or video consultation. The participant will complete an online registration form, which records their medical history and cardiac risk factors. A paper-based manual is available for participants who are unable or unwilling to use the online rehabilitation system.^13^ The website generates a tailored plan from this information, consisting of individualised goals for exercise, diet (eating more fruit and vegetables and reducing salt), emotions (managing stress, anxiety and low mood) and smoking. Adherence to these goals is regularly assessed by a short set of questions and feedback on performance. As the participant progresses through the programme, goals become increasingly difficult. Each participant records details of their daily exercise in an online diary, and regular feedback is given. Smokers are provided with feedback about the amount of money they are saving. The programme also contains written information about the health consequences of heart disease and risk factors (exercise, diet, sexual activity, driving, returning to work, hobbies, holidays, benefits, smoking, anxiety and mood). In addition, the programme reduces negative emotions by providing advice about stress reduction and anxiety management skills. There is access to an online discussion forum, and ‘ask the expert’ email facility. Cardiac rehabilitation staff can monitor participants’ progress and respond to questions posted via email. After 12 weeks, the cardiac rehabilitation staff member will see the participant again to discuss progress and local exercise opportunities. Cardiac rehabilitation staff will report any safety events that they become aware of.

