**Table 2 T2:** ACTIVATE protocol schedule of forms and procedures

Procedures	Screening	Baseline/randomisation	7 days postrandomisation*	Trial intervention†	26 weeks postrandomisation	27 weeks postrandomisation*	52 weeks postrandomisation	53 weeks postrandomisation*
Eligibility screening and consent								
Assessment of eligibility	X							
Informed consent	X							
Confirm consent		X		X	X		X	
Randomisation		X						
Vital signs, height, weight, serum cholesterol		X						
Outcome measurement								
Seattle Angina Questionnaire		X			X		X	
MRC dyspnoea scale		X			X		X	
Hospital Anxiety and Depression Scale		X			X		X	
General Self-Efficacy scale		X			X		X	
EQ-5D-5L		X			X		X	
Client Service Receipt Inventory		X			X		X	
Physical activity measured with ActivPal accelerometer		X	X*		X	X*	X	X*
International Physical Activity Questionnaire			X			X		X
Incremental shuttle walk test		X			X		X	
Safety event reporting								
Monitoring of adverse events			X	X	X	X	X	X
Monitoring of serious adverse events			X	X	X	X	X	X

*Removal of ActivPal after 7 days.

†If randomised to intervention arm, participants will be invited to meet with member of cardiac rehabilitation staff who will train the participant on how to use the intervention.

EQ-5D-5L, EuroQol-5 Dimensions-5 Levels.

Qualitative interviews will take place with a selection of participants at the end of the 12-week cardiac rehabilitation programme among those receiving the intervention, and between months 11 and 12 with the same sample of participants in the intervention group and an additional sample from the control group. These will gather data on trial participation and intervention design (see the ‘Process evaluation’ section).

Routinely collected demographic, clinical and recruitment data will include the number of participants who are eligible, willing to be randomised, withdraw after randomisation, complete outcome measurements, reasons for non-completion, age and gender.

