#### Blinding

This is a pragmatic trial comparing the ‘Activate Your Heart’ cardiac rehabilitation intervention with usual care, so it will not be possible to blind participants or their rehabilitation providers to treatment group allocation. However, collection of outcome measures and data analysis will be performed blind to treatment allocation. We will include a perception of allocation form for the person collecting the outcome measures to complete, to monitor the level of blinding achieved for these researchers.

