### Ethics and dissemination

NHS research ethics approval was obtained from North of Scotland Research Ethics Committee, reference 21/NS/0116. The current protocol is version 5 (4 May 2023). Participants will provide written informed consent. A trial steering committee is providing overall supervision, and an independent data safety and monitoring committee is responsible for reviewing and assessing recruitment, interim monitoring of safety and effectiveness, trial conduct and external data.

All safety events will be recorded by researchers when they are made aware of the event by the participant, treating clinician or therapist. Adverse event reports and serious adverse events (SAEs) not related to the intervention will be entered on to the remote data entry system. Each SAE will be assessed by the relevant PI to determine whether it is related to the intervention. A related SAE will be assessed by the CI to determine whether it is expected. If the SAE is related and unexpected it will be reported to the research ethics committee and sponsor in an expedited manner.

Reporting of the trial will be consistent with the Consolidated Standards for Reporting Trials (CONSORT) 2010 Statement (patient-reported outcomes and non-pharmacological interventions).^35^ We will submit the final report to a peer-reviewed academic journal, according to our publication strategy and authorship policy. Research data will be available for secondary analysis on reasonable request.

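### By-arm counts of non-serious safety events are open to ascertainment bias, because only the intervention arm has a therapist reporting route and monitoring during the programme

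*Protocol article*

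**What the plan says.** The protocol article describes safety collection in three places.

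- **Cardiac rehabilitation intervention.** Intervention participants have staff contacts that control participants do not. There is a training contact: "Before beginning the programme, each participant sees a member of cardiac rehabilitation staff who provides training on the website". There is a later review: "After 12 weeks, the cardiac rehabilitation staff member will see the participant again to discuss progress and local exercise opportunities". In between there is an open channel: "Cardiac rehabilitation staff can monitor participants’ progress and respond to questions posted via email". The section ends with a reporting instruction: "Cardiac rehabilitation staff will report any safety events that they become aware of".
- **Outcomes, Table 2.** The row "Monitoring of adverse events" and the matching row for serious adverse events are marked at 7 days and at 26, 27, 52 and 53 weeks. Both are also marked under the trial-intervention column, whose footnote reads "If randomised to intervention arm, participants will be invited to meet with member of cardiac rehabilitation staff".
- **Ethics and dissemination.** "All safety events will be recorded by researchers when they are made aware of the event by the participant, treating clinician or therapist".

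The Blinding section adds that "it will not be possible to blind participants or their rehabilitation providers to treatment group allocation". The article describes no matching contact for the control arm.

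**The concern.** A count of safety events reflects how often events occur and how many reach the record. Here the second factor differs by arm. The intervention arm has one more source of reports (the therapist) and one more marked monitoring column, and both fall in the stretch when control participants have no scheduled safety contact.

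The Introduction names the harms of interest as injury and angina provoked by exercise. Many such events would be non-serious, and these are the most sensitive to whether someone happens to hear of them. Unequal collection could make equal true rates look like an excess with the programme. The counts will be read: the data safety and monitoring committee reviews safety, and the process evaluation examines adverse events as unintended consequences.

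**Working it through.** **Step 1. Routes by which an event can reach the record**

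| Route | Control | Intervention |
|---|---|---|
| Participant report | yes | yes |
| Treating clinician report | yes | yes |
| Therapist report | no | yes |
| Table 2 points common to both arms (day 7; weeks 26, 27, 52, 53) | 5 | 5 |
| Table 2 trial-intervention column | 0 | 1 |

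Control therefore has 5 marked monitoring points and the intervention arm has 6. The sixth covers at least two staff contacts plus email.

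**Step 2. Where the gap falls**

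From day 7 to week 26 is 26 − 1 = 25 weeks. The article says that the programme can be completed in 8 weeks and places the staff review after 12 weeks. Both lie inside the gap. The training contact precedes the programme and can reveal little about it, so any effect comes mainly from the review and the continuing channel.

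**Step 3. Direction**

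Let *p* be the true risk of a non-serious event, equal in both arms, and *d* the probability that it is recorded through the shared routes. Let *s* be the share of otherwise missed events that the extra route picks up.

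- Control, observed: *p* × *d*
- Intervention, observed: *p* × [*d* + *s*(1 − *d*)]
- Spurious risk ratio: 1 + *s*(1 − *d*)/*d*

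The ratio cannot fall below 1 and does not depend on *p*. This holds if reporting through the shared routes is otherwise the same in both arms.

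**Step 4. Size, on assumed values**

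The article gives no detection rates, so *d* and *s* are assumptions. The ratios are:

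| *d* | *s* = 10% | *s* = 25% | *s* = 50% |
|---|---|---|---|
| 50% | 1.10 | 1.25 | 1.50 |
| 70% | 1.04 | 1.11 | 1.21 |
| 90% | 1.01 | 1.03 | 1.06 |

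The number of extra participants with an event needs an arm size. The Sample size section gives 207 per group, and 207/0.80 = 258.75, which rounds up to the stated 259.

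Middle case, with *p* = 30% (assumed), *d* = 70% and *s* = 25%:

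- Intervention detection: 0.70 + 0.25 × 0.30 = 0.775
- Observed risks: 0.30 × 0.775 = 23.25% against 0.30 × 0.70 = 21.0%
- Ratio: 0.775/0.70 = 1.11
- Extra participants with an event: 259 × 0.0225 = 5.8, about 6

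At the same *p*, the corners of the table run from 259 × 0.30 × 0.01 = 0.8 to 259 × 0.30 × 0.25 = 19.4 extra participants.

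**The case against.** Several stronger readings are tempting, and the article does not support them.

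- **A harms endpoint is biased.** The article names none. The objectives, Table 1 and the Statistical analysis section contain no safety outcome and no between-arm test of events. What is exposed is any comparison of recorded counts. The article also does not say in what form the monitoring committee sees them.
- **Control events are captured only at five visits.** Participants and treating clinicians can report at any time in both arms, and all participants are seen by their general practitioner or cardiology team to optimise usual care. Control lacks the therapist route and a scheduled contact between day 7 and week 26, but it does not lack reporting.
- **Every staff contact is a safety enquiry.** The instruction is passive: staff pass on what they learn. Nothing says that they ask.
- **The distortion is large.** Assumed capture of 60% against 85% gives 0.85/0.60 = 1.42, and 50% against 85% gives 1.70. These need the extra route to recover 0.25/0.40 = 62.5% and 0.35/0.50 = 70% of missed events, which is a lot for passive reporting.

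It is also fair to say that angina frequency (SAQ-UK) and health service use are collected alike in both arms at 6 and 12 months. This helps, but neither counts minor events during the programme weeks.

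Finally, event tabulation commonly belongs in the full protocol or SAP, which are not shown. That is right as to tabulation. The point rests on something else: the article itself states an unequal collection scheme, and an SAP rule can separate the sources only if the source was recorded.

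**Conclusion.** The point holds in a limited form. As written, the collection scheme gives unequal ascertainment of non-serious events, in the direction of more recorded events with the programme, and nothing in the article offsets it. The direction rests on otherwise equal reporting through the shared routes.

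The size is unknown. Assumed detection rates give ratios from about 1.0 to 1.5, and a middle case of 1.11. Deaths and admissions should be little affected, since they depend far less on contact with a therapist. The primary outcome and the sample size are not affected. Staff reporting protects participants and is not the fault; what needs care is how the counts from the two arms are set against each other.

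**What to change.** 1. Record the source of each safety report: participant at a scheduled visit, clinician, or therapist. If the case report form already holds this, only the steps below remain. At submission 68 of 518 participants had been recruited, so the field could still be added for most of the trial.
2. Report all events by arm, and keep every serious adverse event in that comparison. Moving therapist-only events out of the main table could hide real harm from the programme.
3. Add a like-for-like comparison of non-serious events elicited by the same questions at the common time points (day 7 and weeks 26, 27, 52 and 53), with therapist-only events shown separately. Use it to interpret any arm difference in non-serious events.

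Safety recording, relatedness assessment and expedited reporting stay unchanged, and no visits are added. The cost is one data field and one table. The restricted comparison uses fewer events. It also does not fully equalise recall, because talks with staff may prompt intervention participants to mention more at later visits.
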